### Fidelity patient sample

Participants in the fidelity study will include both UAIHC patients and members of the UAIHC clinic team. On fidelity assessment sample days (a single randomly chosen day of the last week of the data collection month; see data collection procedures below), participants will be recruited and enrolled from all patients who enter the UAIHC waiting room. It is anticipated that approximately 180 patients will consent to participation across the two-year study period. The inclusion/exclusion criteria for this sample are identical to those used for the outcomes sample with the exception that patients who are currently pregnant will be allowed to participate in this sample.

At check in on the fidelity data collection day, front desk staff will make a printed handout available describing a “How is UAIHC Doing?” evaluation, and asking all patients seen that day to provide feedback through an online questionnaire after that day’s visit. Interested patients will supply their e-mail address and check a box on the printed handout expressing permission to receive the online questionnaire. The UA Study Coordinator will send all interested patients an e-mail with instructions and a link to the secure URL address for the fidelity informed consent form and the Web-based questionnaire. Patients preferring to complete the questionnaire on paper will have the opportunity to receive a hard copy from the front desk (or by mail) with instructions to place completed questionnaires in a secure box at the clinic (or to return them using the enclosed self-addressed stamped envelope). Digitally-signing the informed consent form, or returning a signed paper-based consent form will constitute completion of the informed consent process for fidelity. Patients who complete the questionnaire within 10 days will receive a $10 gift card.

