### Data Collection

For the outcomes evaluation, data will be collected from patient charts and self-reports at four intervals—baseline (initial clinic visit), and at 3-, 6-, and 12-month follow up periods. Participants will receive a reminder email one week before each data collection due date. Baseline data will be due within one week of enrollment. In the email they will be directed to a secure website where they can access and complete the outcomes data collection instrument. If participants have not entered their data within 3 days of their due date, they will receive another reminder email, and those who have not entered their data within another 3 days of their due date will receive a call from the UA Study Coordinator. Healthcare utilization and cost data from healthcare claims will be obtained from their employer with study participant consent. These data will be collected for one year before and one year after clinic enrollment approximately 3 months after the 12-month follow up period to allow time for all incurred claims to be recorded. De-identified claims data for the comparison groups will be collected for the same period of time with “baseline” being defined by the average start date of study participants.

Because the intervention may change over time as clinic operations start up and mature [21], fidelity monitoring data will be collected monthly from study start for 6 months, then quarterly for 6 months, and then semi-annually. Patient-reported fidelity data will be gathered on a single randomly chosen day of the last week of the data collection month from all patients seen at the UAIHC clinic that day. This day will be selected by the UA research team using a simple computer generated randomization scheme and delivered to the UA Study Coordinator the week before the data collection week. A self-administered patient version of the “How is UAIHC doing?” questionnaire will be used for patients. For clinic personnel, fidelity data will be collected during the last week of each fidelity data collection month using an online self-administered practitioner and staff version of the “How is UAIHC doing?” questionnaire. Data from audits of randomly selected, de-identified patient charts and of administrative records will also be used to assess indicators of model implementation.

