### Analysis

Five sets of inter-related analyses are planned for these data. The first will be a descriptive study based on the demographics and baseline values of the first patients (e.g., first 200) who join the study. The purpose of this study and report is to document the characteristics, diagnoses, symptoms and expectations of those patients who choose to enroll in this integrative primary care clinic. Where possible, patient characteristics, diagnoses and symptoms will be compared to those seen nationally and statewide in primary care using data from the National Ambulatory Medical Care Survey (NAMCS) [77]. Basic descriptive statistics will be used. When comparisons are possible, will utilize *t* tests for independent samples for continuous data, and χ^2^ tests for frequencies.

The second analysis will use the fidelity monitoring data to describe clinic operations and to describe how this IM primary care clinic developed over time. Since these are measures of the intervention itself (the clinic), by design the patient fidelity sample measurements over time will not be taken on the same individuals. Therefore, data will be analyzed using simple descriptive statistics. The results will also be examined for trends using regression analysis with time (either continuous or as a set of dummy variables) as the main explanatory variable, and significant *t* tests for the time coefficient(s) as an indication of significant change over time in clinic operations. Components of the clinic model that change significantly over time and/or that contribute to the outcomes will be considered as covariates in the two outcomes studies described below [24].

The third analysis will involve data from the case study participants. The narrative data from the transcribed, audiotaped semi-structured interviews will be content analyzed using dedicated qualitative data analysis/text management software (*Atlas-ti*), and key concepts will be categorized into salient themes and patterns. Those results will be related to each participant’s reported and recorded outcomes to look for insights into clinic impacts and operations.

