The fourth and fifth analyses will be the main outcome studies. The fourth study will be a prospective cohort study of the changes in outcomes from baseline to one year for all patients in the outcomes sample. The primary outcome for this analysis will be health-related quality of life measured in three ways (SF-6D [78], and the physical and mental component summary scores, all derived from the SF-12), with the other outcomes as secondary measures. The main comparison will be baseline to 12-month outcomes and the univariate analyses will use paired *t* tests for continuous data, and use the McNemar test for frequencies [79]. The data will also be examined for patterns of change over time in key outcomes, and the determinants of those patterns, using hierarchical linear modeling (HLM) techniques [80-82]. Fidelity measures with significant changes over time will be used as covariates [24] in these models, as well as other explanatory variables such as demographics, participants’ membership level and baseline diagnoses. If participant numbers for each of the five targeted condition allow, condition-specific outcomes will be examined for each. These same analyses will be applied to other secondary outcomes such as CVD event [70] and mortality [71] risk.

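### Fidelity analysis: if time is dummy-coded and any significant coefficient counts, an unchanged measure is flagged as changed about 27% of the time instead of 5%; one clause also selects covariates on the outcomes

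*Protocol article*

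**What the plan says.** The second analysis (Analysis section) starts with descriptive statistics and then looks for trends by "regression analysis with time (either continuous or as a set of dummy variables) as the main explanatory variable". The criterion for change is significant *t* "tests for the time coefficient(s) as an indication of significant change over time in clinic operations". The text does not say how many coefficients must be significant. It names no joint test and does not say which coding of time applies when.

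The timing is in the Data Collection section: "fidelity monitoring data will be collected monthly from study start for 6 months, then quarterly for 6 months, and then semi-annually". The Fidelity patient sample section expects that "approximately 180 patients will consent to participation across the two-year study period", and the Analysis section adds that "by design the patient fidelity sample measurements over time will not be taken on the same individuals".

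The result is then carried forward. The second analysis says: "Components of the clinic model that change significantly over time and/or that contribute to the outcomes will be considered as covariates". The fourth analysis says: "Fidelity measures with significant changes over time will be used as covariates", referring to its hierarchical linear models (HLM). The fifth analysis includes fidelity measures with significant change over time in its HLM models of utilization and cost. Neither the fourth nor the fifth analysis admits a measure because it contributes to the outcomes.

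**The concern.** With a continuous time term there is one coefficient and one test, so a significant *t* test has its nominal error rate. With dummies, each coefficient compares one wave with the reference wave. Reading the individual *t* tests as evidence of change then makes several attempts per measure at the nominal level. A clinic whose operations did not change would too often be described as having changed, and unrelated fidelity measures would enter models meant to explain the pattern of change in outcomes and costs.

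The clause on contribution to the outcomes is a separate fault that needs no simulation. A covariate chosen because it is associated with the outcome, and then interpreted as a determinant of that outcome in the same data, has an overstated association and a p-value that no longer means what it says.

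**Working it through.** The protocol states no error rate for this rule, so there is no figure of its own to reproduce.

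**Inputs**
- Waves (Data Collection): 6 monthly + 2 quarterly + 2 semi-annual over two years = 10, at about months 1–6, 9, 12, 18 and 24. The count is derived, not stated.
- Coefficients under dummy coding: 10 − 1 = 9.
- Patients per wave: 180 / 10 = 18 if spread evenly (assumption).
- Different patients at each wave (Analysis section).
- Alpha .05, two-sided. The article states .05 only for the cost sample size, so using it here is an assumption.
- Decision rule: a measure is flagged if any of the nine *t* tests is significant. The word *any* is not in the text. It is the natural reading, since no other count is given.
- Patient dimensions (Fidelity monitoring measures): access, whole person care, self-care and wellness, communication style, shared decisions, trust, empathy and partnership = 8, leaving out socio-demographics.

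**Per-measure error rate**

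For wave j against wave 1, t_j = (mean_j − mean_1) / sqrt[s²(1/n_j + 1/n_1)], on 180 − 10 = 170 degrees of freedom. The nine tests share wave 1, so with equal waves they correlate at 0.5. Treating them as independent would give 1 − 0.95⁹ = 37.0%, which is too high. The dependence was therefore simulated with no true change (200,000 runs for the any-dummy rule, 20,000 for the comparison tests):

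| Rule | Chance of flagging an unchanged measure |
|---|---|
| Any of 9 dummy *t* tests, 10 waves of 18 | 26.6% |
| Same, 8 / 9 / 11 / 12 waves of 18 | 22.9 / 24.9 / 28.4 / 30.1% |
| Same, 10 uneven waves totalling 180, small first wave (9 rising to 27) | 21.4% |
| Same, large first wave (27 falling to 9) | 30.4% |
| Joint F test of all 9 dummies | 5.0% |
| Single linear trend | 5.0% |
| Try both codings, flag on either | 28.7% |

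**Expected false flags if all eight patient dimensions were unchanged**
- Any-dummy rule: 8 × 0.266 = 2.1.
- One test per dimension: 8 × 0.05 = 0.4.

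**Which covariates are admitted**

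Second analysis: significant change over time, and/or contribution to the outcomes. Fourth and fifth analyses: significant change over time only. The second analysis is wider, and the extra route uses the outcome data.

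**The case against.** The 27% belongs to one branch of the rule. The same sentence allows continuous time, where the rate is 5%, and the text nowhere says that any one dummy suffices. That stands, so the figure must be given with its conditions. It does not remove the point, because the dummy branch is explicitly allowed and trying both codings gives 28.7%.

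A reader might infer that about 20 false covariates would enter the models (51 patient items plus 27 practitioner items, 78 × 0.26 = 20.3). The documents do not support this:
- They speak of components and measures, and never of testing each item singly.
- The 51 items include socio-demographics.
- The 27 practitioner items are answered repeatedly by the same 15–20 staff, so the rate for independent samples does not carry over directly. With 18 staff and ordinary regression it is 12.7% at a within-person correlation of 0.3 and 4.7% at 0.5. A repeated-measures model brings it back to 26.6%.
- The count also needs every item to be unchanged, whereas the article expects a new clinic to evolve.

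A reader might also infer that the main results are at risk. They are not shown to be: the paired *t* and McNemar tests and the bootstrap cost differences do not use fidelity covariates.

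It can be said that time coding and joint testing are left to an analysis plan that is not shown. That would hold if the article were silent, but it names the test and the criterion. Finally, the second analysis only says that components will be considered. That softens the outcome clause but leaves it at odds with the fourth and fifth analyses.

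**Conclusion.** The point holds in a limited form. If time is dummy-coded over about 10 waves, any significant coefficient counts, alpha is .05 and patients differ between waves, an unchanged measure is flagged about 27% of the time (roughly 21% to 30% over plausible wave counts and sizes). One test of time holds this at 5%. On the eight patient dimensions the inflation amounts to about two false flags instead of fewer than one. These affect the account of how the clinic developed and the HLM models of outcomes and costs, not the main comparisons. The outcome-based route to covariate selection is a fault independent of these figures, and it is inconsistent with the later analyses in the same section. The point should be corrected, but it does not threaten the primary estimates.

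**What to change.** In the second analysis, fix the coding of time in advance and use one test of time per questionnaire dimension or chart indicator: the linear-trend coefficient or, if dummies are used, a joint F test of all wave dummies. Individual dummy coefficients can still be reported descriptively. Delete the clause admitting components that contribute to the outcomes, so that the second analysis agrees with the fourth and fifth. For the practitioner questionnaire, apply the same single test within a model that allows for repeated answers from the same staff.

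Holm or false-discovery-rate control across measures is optional: in screening covariates, missing a real drift may cost more than keeping an irrelevant one.

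The cost is a few sentences of wording and no new data. The downside is that some weak drifts, or changes confined to a single wave, will not be flagged.

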### Outcomes sample

Only patients who are members at UAIHC and who meet the inclusion/exclusion criteria are eligible to enroll in this study. Participation in the study will continue for at least one year after enrollment. It is anticipated that at least 500 patients will consent to participation during the first nine months of the study. Our primary outcome for our main analysis is change in total costs (see the Analysis section below). Using the standard deviation seen in a set of healthcare utilization data from a related group, a sample size of 200 patients should be sufficient to detect a small effect size (Cohen’s d = .20) difference in total costs at a .80 power using an alpha of .05. Therefore, our expected sample size of 500 may also allow for some subgroup analysis. Inclusion criteria: 1) Enrollment in primary care (members) at UAIHC; and, 2) adults ages 18 or older. Exclusion criteria: 1) currently pregnant at time of recruitment; 2) patients who attend the UAIHC clinic as “consultation-only” patients; and, 3) significant cognitive impairment to the extent that the individual is unable to understand the consent and respond to questionnaires.

All new patients will be advised by their primary care physician that they may be eligible to participate in a study to evaluate the effectiveness of the UAHIC. Prior to checkout, patients have an exit session with the University of Arizona (UA) Study Coordinator. During this session (or if necessary, through a follow-up phone call), the Study Coordinator will explain the nature of the study and make a determination of study eligibility, and if appropriate, consent the patient. Patients who joined the UAIHC before study start (July 2013) will also have the opportunity to participate. The study will be explained at their first UAIHC visit after study start.

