### Fidelity monitoring measures

#### Patient feedback questionnaire

Patient experiences of the various dimensions of integrative medical care will be assessed for their same-day care by a 51-item “How is UAIHC doing?” Patient Version questionnaire developed for the fidelity study. Dimensions of the questionnaire include access to care, whole person care, promotion of self-care and wellness, practitioner communication style, shared decision-making, trust in the practitioner, perceived practitioner empathy, perceived health partnership, and socio-demographic information. Items were derived from established measures of primary care quality: the Consumer Assessment of Healthcare Providers and Systems (CAHPS) Surveys 2.0 Adult visit and Patient-Centered Medical Home versions [50,57], the Ambulatory Care Experiences Survey (ACES) [73], and the Consultation and Relational Empathy measure (CARE) [74]. Several items were developed for the study to tap patient experiences of IM care not assessed in existing instruments. It is estimated that it will take 10–15 minutes for patients to complete this questionnaire.

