### Patient chart extraction

A number of items will be extracted from a random sample of 10 de-identified patient charts at the end of each fidelity measurement month for patients seen during that month. The clinic staff will generate a list of the medical record numbers of all enrolled patients seen during the last month and report the total number (N) to the research team. The research team will use a simple computer-based randomization scheme to create an equal length list consisting of “select” and “don’t select” statements. Clinic staff will then match these lists and pull and de-identify those charts whose medical record numbers match up with the “select” statements. The data to be extracted by the research team are intended to assess IM whole person care (e.g., a review of systems beyond those typically assessed in conventional care including domains such as spirituality, social support, family and work stressors, etc.), the patient-practitioner partnership agreement, the mix of conventional and CM therapies used, and lifestyle recommendations over the past month. Visit lengths are also recorded.

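### A significant time slope in the fidelity regression cannot be attributed to clinic operations for visit-dependent survey and chart items, because the mix of first and follow-up visits is likely to shift as membership builds

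*Protocol article*

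**What the plan says.** In the protocol article, Analysis, the second analysis examines the fidelity data by "regression analysis with time (either continuous or as a set of dummy variables) as the main explanatory variable". Significant t tests are taken "for the time coefficient(s) as an indication of significant change over time in clinic operations". The section notes that "by design the patient fidelity sample measurements over time will not be taken on the same individuals", because the measures describe the clinic and not a cohort.

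Data Collection takes the patient survey on one randomly chosen day per wave "from all patients seen at the UAIHC clinic that day". Under Patient feedback questionnaire, experiences "will be assessed for their same-day care". The chart audit draws "from a random sample of 10 de-identified patient charts at the end of each fidelity measurement month for patients seen during that month" (Patient chart extraction). It covers a broad review of systems, the partnership agreement, the therapy mix, lifestyle recommendations and visit length.

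Study design describes the clinic as new and still developing. Under Outcomes sample, "It is anticipated that at least 500 patients will consent to participation during the first nine months of the study"; the same section says that patients who joined before July 2013 may also take part, without giving their number. The fourth and fifth analyses use fidelity measures with significant change over time as covariates in the hierarchical linear models (HLM).

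**The concern.** Reading a time slope as a change in the clinic requires the sampled visits to be comparable across waves. Each member has one first visit, while follow-up contacts accumulate with membership. The waves are densest while the clinic is filling: monthly for six months, then quarterly, then semi-annual. First visits are therefore likely to make up a falling share of the sample. An item recorded more often, or a visit that runs longer, at intake would then decline on average even if the clinic worked in exactly the same way throughout. Coding time as dummy variables does not help, since the dummies absorb the same shift.

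Three results are exposed: the account of how the clinic evolved, the quality feedback to staff, and the choice of fidelity covariates for the HLM models.

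**Working it through.** The plan gives no power or error rate for the trend test, so there is no figure of its own to reproduce.

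**Inputs from the document.** Six monthly, two quarterly and two semi-annual waves make 10, placed here at months 1–6, 9, 12, 18 and 24. About 180 fidelity patients (Fidelity patient sample) give 180/10 = 18 per wave. Ten charts per wave give about 100.

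**Assumed inputs.** The document does not give the first-visit share at each wave, or the difference *d* (in SD) between first and follow-up visits.

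**Hand check.** With no change in the clinic, the expected slope is *d* × (slope of the first-visit share on time). Let the share fall linearly from 60% to 10% over 23 months, with *d* = 0.8.
- Bias = 0.8 × 0.50/23 = 0.0174 SD per month, or 0.40 SD over the study.
- Mean month = 84/10 = 8.4. Sum of squares = 18 × (1216 − 10 × 8.4²) = 18 × 510.4 = 9187.
- Mean of p(1−p) over waves is 0.222, so residual variance ≈ 1 + 0.64 × 0.222 = 1.142.
- SE = √(1.142/9187) = 0.0112, and the ratio is 1.56.
- Chance of p < 0.05 ≈ 1 − Φ(1.96 − 1.56) = 0.34.

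**Simulation of the stated test.** Linear regression on month, two-sided t test at 0.05, clinic unchanged, 4,000 runs per cell. Ranges cover a linear fall and a fall completed by month 9.

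| First-visit share | Sample | d = 0.2 | d = 0.5 | d = 0.8 | d = 1.5 |
|---|---|---|---|---|---|
| constant 50% | survey, 180 | 5% | 5% | 5% | 5% |
| 40% to 20% | survey, 180 | 5% | 6–7% | 8–9% | 18% |
| 60% to 10% | survey, 180 | 7% | 17–18% | 35% | 73–75% |
| 80% to 5% | survey, 180 | 9–10% | 31–33% | 66–67% | 98–99% |
| 60% to 10% | charts, 100 | 6% | 11% | 20–23% | 46–50% |
| 80% to 5% | charts, 100 | 8% | 19% | 41–42% | 83–85% |

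The hand check agrees with the 35% cell. With a first-visit indicator added (*d* = 0.8), the rate is 4.5–5.6% in every scenario.

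**Tying the share to accrual.** First-visit share = new per month / (new per month + members × contacts per month).
- The 500 consents may include existing members, so I split them as 0 + 500, 100 + 400 and 200 + 300 (existing + new). New patients arrive evenly over nine months, then at half that rate.
- The membership tiers (Intervention) cover 5+2+2 = 9, 10+4+4 = 18 and 20+8+8 = 36 contacts. If a bundle lasts a year (assumed), the lower two give 0.75 and 1.5 contacts per month.
- The item is delivered at 80% of first visits and 30–50% of later ones (assumed).

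| Existing members | Month-1 share | Survey, 180 | Charts, 100 |
|---|---|---|---|
| 0 | 57–73% | 15–59% | 10–37% |
| 100 | 20–33% | 7–21% | 6–14% |
| 200 | 9–17% | 6–10% | 5–8% |

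If intake stops at month 9, the upper survey figures rise to 69%, 28% and 12%. With a first-visit term, rates are about 5–7% throughout. The chart column treats charts as a sample of visits. Sampling patients seen in the month, as the audit does, gives 8–29% with 100 existing members and 6–12% with 200.

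**The case against.** - **The rule is narrower than it may look.** A reader might infer that any slope counts as change, or that an unchanged clinic is bound to appear to drift. The Analysis section requires significance and calls it an indication. The simulated rates run from nominal to near certainty on inputs that the document does not give. This stands.
- **Members from before July 2013 dilute the shift.** They exist, and the 500 consents may include them. This stands, and it is why the lower rows of the accrual table matter.
- **The main comparisons are safe.** A reader might infer that a visit-mix artefact contaminates the main outcome results. It does not. The baseline-to-12-month comparison uses paired t and McNemar tests, and the between-group cost changes are bootstrap mean differences. Neither uses a fidelity covariate; those enter only the HLM models.
- **Not every item is visit-dependent.** Survey domains such as empathy, trust and access have no stated link to first visits. A partnership agreement looked for anywhere in the chart would not fall. The staff survey covers the entire staff and is untouched. This stands.
- **Other terms are not excluded.** Time is the main explanatory variable, not the only one, and the forms are not shown. But no other term is named for this analysis, whereas the HLM models do list covariates. A later plan can add the term only if visit type is recorded.
- **A changed mix may be real change.** The therapy mix is itself an audited item. This stands against adjusting by default for practitioner type. It does not explain why fewer intake visits should count as a change in how the clinic works.

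**Conclusion.** The point holds for patient-survey and chart-audit items that depend on visit type, visit length and whole-person review of systems being the likeliest. For these, a significant time coefficient does not by itself show a change in operations.

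The false-signal rate stays near 5% if many members joined before study start or the item differs little by visit type. It is well above 5% if few joined earlier and the item differs strongly. First-visit shares, contact rates and visit-type differences are all assumptions, and the document does not itself state that the mix will shift. It is a likely consequence of a new clinic's accrual and of sampling whoever attends. The matter is worth correcting for the description of the clinic, the staff feedback and the choice of HLM covariates, and no further.

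**What to change.** Record first versus follow-up visit on the patient questionnaire and the chart form. Add it to the trend regression, or fit the trend separately by visit type, and report the adjusted trend beside the unadjusted one. Call a slope a change in operations, and pass the measure on as a candidate covariate, only if the slope persists within visit type.

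Do not adjust by default for practitioner type or months since joining; keep these as sensitivity analyses. A shift in therapy mix may be real change, and tenure tends to rise with calendar time in a new clinic.

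The cost is one form item, if it is not already there, and slightly wider intervals. For an item unrelated to visit type at survey size, SE inflation is 1/√(1 − R²), where R² is the share of variation in the first-visit indicator explained by month. A linear fall from 60% to 10% gives R² ≈ (0.50/23)² × 51.04 / (0.439 × 0.561) = 0.10, so about 5% wider. A fall from 80% to 5% gives R² ≈ 0.22, so about 13% wider.

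### Patient fidelity questionnaire: the planned trend test appears to leave day-to-day variation out of its error, although each wave is one clinic day

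*Protocol article*

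**What the plan says.** All references are to the protocol article.

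- **Sampling (Data Collection).** Patient fidelity data come from "a single randomly chosen day of the last week of the data collection month from all patients seen at the UAIHC clinic that day". The schedule is "monthly from study start for 6 months, then quarterly for 6 months, and then semi-annually".
- **Size (Fidelity patient sample).** "It is anticipated that approximately 180 patients will consent to participation across the two-year study period". Recruitment is open to everyone who enters the waiting room on the sampled day. Nothing excludes a patient who answered in an earlier wave.
- **Test (Analysis, second analysis).** The stated reason for simple methods is that "by design the patient fidelity sample measurements over time will not be taken on the same individuals". Trends are then examined by "regression analysis with time (either continuous or as a set of dummy variables) as the main explanatory variable", and significant t tests of the time coefficient(s) are taken "as an indication of significant change over time in clinic operations".
- **Use of the result (Analysis).** The second analysis says that components which change significantly, or which contribute to the outcomes, will be considered as covariates. The fourth analysis is firmer: "Fidelity measures with significant changes over time will be used as covariates". The fifth analysis likewise includes them in its HLMs for cost and utilization.

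**The concern.** The question is whether the clinic changed over time, and the unit sampled to answer it is the day. Patients seen on one day share its staffing, load and incidents, so their answers may resemble each other more than answers from different days. That day-to-day variation belongs in the error of a trend test. The article's argument rules out one kind of dependence, the same person measured repeatedly, and does not mention the other, different people measured on the same day. Taken at its word, it leads to a regression on about 180 patients treated as independent, when the information about time comes from about 10 days.

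The dummy-variable option has a further problem. With one day per wave, each wave's dummy is also that day's dummy. Day and time are fully confounded, and no between-day error term exists with which to test them.

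Two things are at stake. Describing how the clinic developed is an aim in its own right, so a false trend is a false finding. Significance over time also decides which fidelity measures enter the HLMs of the fourth and fifth analyses.

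**Working it through.** **Inputs**

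- Waves: 6 monthly + 2 quarterly + 2 semi-annual = 10 days in two years, taken as months 1–6, 9, 12, 18 and 24 (derived from Data Collection).
- Patients per day: 180 / 10 = 18 (derived from Fidelity patient sample).
- Alpha: .05, two-sided. The article states .05 only for the total-cost sample size. Its use for the fidelity t tests is an assumption.
- Unit of regression: the individual patient, inferred from the article's reasoning and from the dummy option, which cannot be tested on one mean per wave.
- Same-day ICC: not given. Assumed range 0 to 0.20.

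The article states no error rate, power or ICC for this test, so there is no figure of its own to reproduce.

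**Type I error with continuous time**

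The design effect is DE = 1 + (18 − 1) × ICC. The ordinary standard error is too small by a factor of about √DE, so the true type I error is about 2 × [1 − Φ(1.96/√DE)]. Example at ICC 0.05: DE = 1 + 17 × 0.05 = 1.85; √1.85 = 1.36; 1.96/1.36 = 1.44; error = 15.0%.

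The last two columns come from a simulation with no true trend and a random day effect, 10,000 runs per ICC.

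| Assumed ICC | DE | Formula | Simulated, patient-level regression | Simulated, regression on 10 day means |
|---|---|---|---|---|
| 0 | 1.00 | 5.0% | 4.7% | 4.5% |
| 0.01 | 1.17 | 7.0% | 6.8% | 4.9% |
| 0.02 | 1.34 | 9.0% | 9.1% | 5.3% |
| 0.05 | 1.85 | 15.0% | 14.8% | 5.2% |
| 0.10 | 2.70 | 23.3% | 23.7% | 5.0% |
| 0.20 | 4.40 | 35.0% | 36.5% | 5.1% |

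The result is not peculiar to 10 waves. With 8 days of 22 patients the formula gives 10.0% at ICC 0.02 and 26.6% at 0.10.

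**Time as dummies**

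Each single wave-against-first-wave t test has a simulated error of 5.0%, 9.4% and 25.9% at ICC 0, 0.02 and 0.10. Regression on day means is no remedy here: 10 means and 10 parameters leave no degrees of freedom.

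**Power cost of using day means if the ICC is zero**

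A patient-level test on 180 − 2 = 178 df has 80% power at a noncentrality of 2.82. The same noncentrality on 10 − 2 = 8 df, where the critical value is 2.31 instead of 1.97, gives about 69%.

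**The case against.** The strongest reply has five parts.

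- **No ICC is documented.** Much of the questionnaire concerns the patient's own encounter (communication, shared decisions, trust, empathy), and a same-day correlation near zero cannot be excluded. This stands. A reader might infer that false trends will be declared two to five times too often. That multiple holds only for an assumed ICC of about 0.02 to 0.10; it is 1 at zero, 1.4 at 0.01 and 7 at 0.20.
- **The unit and the variance estimator are not stated.** A journal article may leave clustered errors to a fuller analysis plan. This stands in part. The article does give its reason for simple methods, and that reason passes over the day. If a fuller plan already has a day term, the point is met.
- **The number of false trends is unknown.** It is tempting to multiply the error rate by the 51 questionnaire items. The documents do not support that: the items include socio-demographic questions, and the article speaks of components of the clinic model, not item-by-item tests.
- **The dummy option need not mean that any one significant dummy counts as change.** The article states no such rule. Under that rule at least one of nine dummies would be significant in about 27% of runs at ICC 0, but that is multiplicity, not clustering. The confounding of day with wave needs no such rule and remains.
- **The outcome results are largely untouched.** This stands, as set out in the verdict.

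**Conclusion.** The point holds for the patient fidelity questionnaire. It does not extend to the chart audits, which sample patients seen across the month, or to the personnel survey, which measures the same staff again and has a different dependence.

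The direction is firm: if patients are the regression unit, any positive same-day correlation makes the linear time test anti-conservative. The size is conditional, from about 5% at ICC 0 to about 36% at 0.20. It rests on about 10 days of about 18 patients, a two-sided .05 level and the inferred patient-level regression. The confounding of day with wave under dummy coding depends on none of the assumed ICCs.

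The consequences are limited to statements about the clinic's evolution and to the choice of fidelity covariates in the HLMs. Even there, significance over time is not the only route, because the second analysis also admits components that contribute to the outcomes. A reader might infer that the main outcome results are biased. The documents do not support that: the paired t and McNemar tests from baseline to 12 months and the bootstrap cost differences use no fidelity covariate, and no bias in any outcome estimate has been shown.

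**What to change.** For the patient questionnaire:

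1. Test the trend with time as a continuous variable on the day-level means (10 points, 8 df), or fit a patient-level mixed model with a random day effect and small-sample degrees of freedom.
2. Do not use t tests of individual wave dummies as the criterion of change. Wave-by-wave results can still be shown descriptively.
3. Identify repeat respondents where possible, then add a patient effect or keep first responses only. The recruitment rule allows recurrence, although its extent is unknown and is not part of the figures above.
4. Use the result of this test where the fourth and fifth analyses refer to significant change over time.

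No extra sampling days are needed; apart from the identification of repeat respondents, the change is to analysis wording. The price is that fewer trends will reach significance. If the ICC is in fact near zero, an effect that the patient-level test would detect with 80% power is detected with about 69% on the day means. That loss should be acknowledged, since detecting clinic evolution is one purpose of the fidelity data.
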